#### **Treatments used**

Sofosbuvir: 400 mg once daily

Daclatasvir: 60 mg once daily

#### **Treatments that could not be used or use with precaution because of potential drug-drug interactions**

Refer to the respective SmPC daclatasvir and sofosbuvir in Appendix 7 and 8 for drug interaction information in medicinal products and Appendix 9 for the main drug-drug interactions.

## 9. STUDY IMPLEMENTATION

### Study schedule

|                                | Testing phase  | Therapeutic phase for positive HCV RNA | W4 | W8 | W12 | W24            | W28 |
|--------------------------------|----------------|----------------------------------------|----|----|-----|----------------|-----|
| Consent form                   | X              | X                                      |    |    |     |                |     |
| Eligibility criteria           | X              | x                                      |    |    |     |                |     |
| Consultation and clinical exam |                | x                                      | x  | x  | x   | x              | x   |
| HIV RDT                        |                | x                                      |    |    |     |                |     |
| HBs Ag RDT                     |                | x                                      |    |    |     |                |     |
| HCV Ab RDT                     | X              |                                        |    |    |     |                |     |
| HCV RNA plasma                 | x  |                                        |    |    |     | x              |     |
| HCV RNA DBS                    | x  |                                        |    |    |     |                |     |
| AST / ALT                      |                | x                                      | x  | x  | x   | x              |     |
| Creatinine                     |                | x                                      | x  | x  | x   |                |     |
| CBC                            |                | x                                      | x  |    |     | x              |     |
| Pregnancy test     |                | x                                      | x  | x  |     |                |     |
| PT                             |                | x                                      |    |    |     | x  |     |
| Bilirubin                      |                | x                                      |    |    |     | x  |     |
| Albumin                        |                | x                                      |    |    |     | x  |     |
| Fasting glycemia               |                | x                                      |    |    |     |                |     |
| Score APRI / FIB4              |                | x                                      |    |    |     |                |     |
| Liver ultra-sound              |                | x                                      |    |    |     | x  |     |
| Biobank                        |                | x                                      |    |    | x   | x              |     |
| Socio-economic evaluation      | x              |                                        |    |    |     |                |     |
| DAA delivery                   |                | x                                      | x  | x  |     |                |     |
| Adherence assessment           |                |                                        | x  | x  | x   |                |     |

(1) For patients in arm 1

(2) For patients in arm 2

(3) For cirrhotic patients

(4) Pregnancy test will be performed at inclusion, W4 and W8 for all women of childbearing age

## **Patients' participation in the study**

### **Information**

Patient participation in this clinical study is voluntary.

Each potential participant will be informed individually of the purpose, scope of the study, procedures involved, duration of follow-up, potential risks and benefits and any discomfort it may entail. In addition to oral explanations, a written information sheet will be systematically provided in Cambodian language (see Appendix A).

### **Consent**

If the patient accepts to be enrolled in the study, he will write his/her full names clearly, and date and sign the consent form, as will do the investigator (the nurse or the CHW). Written informed consent must be obtained before any exam related to the study. The original copy of the form will be stored in a location that is secure and inaccessible to other clinic employees. Participants may be given, if they wish, a copy of the consent form after they sign.

Consent will be collected in health centres for Arm 1 and directly in the household of participants for Arm 2.

A second specific information sheet and consent form will be used for the therapeutic phase. Consent will be collected in the provincial hospital.

### **Information process for Arm 1**

- The CHWs will be in charge to inform participants in their respective households:
  - o Provide information on the study using information sheet and leaflet
  - o Distribute dedicated voucher including serial number code. These vouchers will be used in HC as identification documents for nurses. One part will be given to participant and one part will be kept by the CHW and stored in health centres

### **Testing phase for Arm 1**

The testing phase for arm 1 will take place in health center. During this visit, the investigator:

- Check to confirm that 1/ the participant is in the list of selected HH (2) the number on the participant's voucher match with the second part.
- Check eligibility criteria
- Collect the written consent form
- Attribute a identification code in the study
- Complete the confidential list including personal information (address, phone number) and keep it in a secured cupboard in the health center
- Fill the screening form
- Perform the HCV RDT on a finger stick capillary whole blood
- Give the result to the participant
- Provide specific counseling to avoid future transmission in case of negative result

- Collect blood sample (5 mL EDTA tube) in case of positive RDT and send it to Provincial hospital laboratory to collect plasma. Plasma will be sent to UHS with the ID number to perform HCV RNA
- Give an appointment to participant to receive the result of HCV RNA

### **Testing phase for Arm 2**

The testing phase for arm 2 will take place directly in the household of participant or in a specific location in the village. During this visit, the CHW:

- Check eligibility criteria
- Provide oral information, information sheet
- Collect the written consent form and give an ID number
- Complete the confidential list including personal information (address, phone number) and keep it in a secured cupboard
- Fill the screening form
- Perform the HCV RDT on a finger stick capillary whole blood
- Give the result to the participant
- Provide specific counseling to avoid future transmission in case of negative result
- Collect DBS (5 spots) on a finger stick capillary whole blood in case of positive RDT and put it in a specific plastic bag with the ID number
- Keep the DBS in HC in the fridge and send to UHS on a regular basis
- Give an appointment to participant to receive the result of HCV RNA

### **Case detection phase**

The results of HCV RNA will be centralized in HCs and nurses will be in charge to give the results.

During this visit, the nurse confirms the identification of the participant and informs the patient of the result of HCV RNA. The nurse will be in charge to confirm the awareness of testing status and to fill the CRF.

#### For negative HCV RNA patients

The nurse will be in charge to explain to the patient that HCV infection has occurred and is cured and don't need any follow-up and exams. The most important point is to explain to the patient that HCV Ab will stay positive for all life without any consequences for him. But re-infection is possible.

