### HCV RNA quantification

WHO suggest that nucleic acid testing for the detection of HCV RNA be performed directly following a positive HCV serological test to establish the diagnosis of chronic HCV infection and that all patients with positive HCV RNA should be assessed for the treatment.

HCV RNA availability in resource-limited setting is challenging. HCV RNA could be done on plasma but requires syringes, tubes, centrifuges machines and skilled human resources. The Cepheid Xpert HCV viral load assay could be an alternative to central laboratory equipped for classical virological diagnosis (23)(24). The limited operator input allows considering an implementation in provincial hospital and a recent article report a good accuracy on finger-stick capillary whole blood (25). However, patient needs to come to provincial hospital, which could increase the risk of lost-to-follow-up after a positive Ab. And the total number of possible samples evaluated each day is limited, which could be challenging for a scale-up strategy.

The performance of the Omunis Generic HCV assay on an open polyvalent PCR platform was recently evaluated in France and Cambodia (26); this HCV PCR assay showed good concordances in clinical specimens when compared to the Roche assay. The cost per test of the Generic HCV assay has been estimated by MSF Access Campaign at \$22.6 including the Arrow automated extraction kit and proteinase K reagent, which is close to the cost per test of the Cepheid Xpert HCV viral load assay estimated at \$18 (27). This affordable HCV test could represent a surrogate method to manufacturer's PCR systems for the diagnosis and monitoring of HCV RNA testing in central laboratories from low- and middle- income countries. It could allow 40 to 82 samples per day and could be used on plasma or DBS (27). DBS could represent an alternative to simplify and decentralize access to HCV RNA, specifically at community level. DBS could easily be sent to equipped central laboratory and HCV RNA performed at this level. The performance seems good but sensitivity seems altered for patients with low-level viremia (28) and HCV RNA degradation could occurred in DBS samples stored at room temperature (29).

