### Common management in the provincial hospital for positive HCV RNA patients

For negative HCV RNA, a specific counseling will be done.

For positive HCV RNA, a consultation in the Provincial Hospital will be planned. In the absence of consultation within 4 weeks, SMS reminder will be sent to participant. A correlation table will be available in the provincial hospital to confirm the identification of the participant. Trained general practitioners will do the consultation with the possible support of hepatologist by phone. The baseline assessment will include questionnaires (risk behaviours and socio-economic status), clinical exam, blood sampling and liver ultrasound.

Symptomatic cirrhotic patients will be defined as patients with at least one of these signs: ascites, collateral circulation of the abdominal wall around the umbilicus, encephalopathy, jaundice, HCC. These patients will be referred to a National Hospital in Phnom Penh to a hepatology unit.

For the others patients, DAA treatment will be proposed, after checking the result of creatininemia and the possible drug-drug interactions.

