### **Visit W28**

This visit will be the last visit of the study. In case of SVR12, patients will be informed of the cure. Recommendations to continue liver ultrasound follow-up every 6 months will be given for cirrhotic patients.

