### HCV RNA viral load

In the arm 1, HCV RNA will be done using the Biocentric Generic HCV assay on plasma. Five mL of whole blood will be collected on EDTA tube. To avoid the risk of HCV RNA degradation during the transportation, whole blood tubes will be sent to Provincial Hospital laboratory first to collect plasma. Then, plasma tube will be sent to the UHS laboratory to perform HCV RNA.

In the arm 2, blood will be collected on DBS. DBS will be packaged in sealable plastic bags with a desiccant until transported to health center. In health center, packaged DBS will be kept in fridge. One time per week, the head of HC or nurse will insert bundled DBS into rip-resistant envelope and give to taxi for transportation to UHS in Phnom Penh. The HCV RNA will be eluted from DBS using DBS elution buffer (PBS, BSA 10%, Tween 0,05%) and manually extracted using the Qiamp Viral RNA Mini kit then amplifies using the Biocentric Generic HCV assay on the BioRad CFX96 thermocycler.

All the samples collected during the screening phase will be destroyed after HCV RNA completion.

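### Every RNA-negative participant is told the infection is cured and needs no exams, but in the community arm this rests on one dried-blood-spot test that may miss low-level virus

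*Protocol*

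**What the plan says.** Section 8 (Common management in the provincial hospital) promises counselling without giving its content: "For negative HCV RNA, a specific counseling will be done". Section 9 (For negative HCV RNA patients) supplies it. The nurse is to "explain to the patient that HCV infection has occurred and is cured and don't need any follow-up and exams", and to add that "HCV Ab will stay positive for all life without any consequences for him". One caveat follows: "But re-infection is possible". The text makes no distinction between arms.

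The specimen does differ between arms. Arm 1 is tested on plasma. For the other arm, section 10 (HCV RNA viral load) states: "In the arm 2, blood will be collected on DBS". The study schedule in section 9 shows one DBS RNA test, in the testing phase. Neither the arm 2 description in section 8 nor section 10 plans a repeat or a plasma confirmation of a negative DBS, and section 10 has all screening samples destroyed once the RNA test is done.

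On DBS, section 3 (HCV RNA quantification) reports: "The performance seems good but sensitivity seems altered for patients with low-level viremia (28" (the closing number is the start of a literature reference). It adds that RNA can degrade in spots stored at room temperature.

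**The concern.** The protocol recognises that the arm 2 test can miss infection at low viral load, then fixes a message that leaves no room for this. A viraemic person with a negative DBS would be told that the infection is over and that no exams are needed. The re-infection warning does not help that person directly, since it concerns a later exposure.

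At stake is individual safety. Someone wrongly told of a cure has less reason to ask for another RNA test if signs of liver disease appear, in an age group that section 3 describes as having a higher risk of advanced liver disease. The trial's comparison is not at stake.

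**Working it through.** The point concerns wording, so the protocol has no figure of its own to reproduce. The first step sets the texts side by side; the second gives a sense of scale only.

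**Step 1: the texts.**
- Evidence: DBS performance seems good overall, with altered sensitivity at low viraemia (section 3).
- Procedure: one DBS test in arm 2, no confirmation of a negative, sample destroyed (sections 8, 9 and 10).
- Message: cured, no follow-up, no exams; re-infection possible (section 9).

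The evidence supports a statement that no virus was found in this sample. It does not support an unqualified statement of cure for every DBS-negative person, and the one caveat does not address a missed infection.

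**Step 2: scale.** Inputs from the protocol:
- 8000 people offered testing, 80 of 160 clusters per arm, so about 4000 in arm 2 (section 14).
- Uptake of 80% in the community arm and 5% antibody positive (section 14).
- Viraemic share of antibody positives: 262/372 = 0.704, or 5.4/6.8 = 0.794 (section 3). Both come from people with HIV and are proxies.

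Assumption: overall DBS sensitivity of 90% to 99%. The protocol gives no value.

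Antibody positive in arm 2: 4000 × 0.80 × 0.05 = 160.
Viraemic: 160 × 0.704 = 112.7, or 160 × 0.794 = 127.1.
Truly RNA negative: 160 − 112.7 = 47.3, or 160 − 127.1 = 32.9.
Missed = viraemic × (1 − sensitivity).
Share of the negative messages that are wrong = missed / (missed + truly negative).

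| Assumed sensitivity | Missed (share 0.704) | Wrong messages | Missed (share 0.794) | Wrong messages |
|---|---|---|---|---|
| 99% | 1.1 | 2.3% | 1.3 | 3.7% |
| 98% | 2.3 | 4.5% | 2.5 | 7.2% |
| 95% | 5.6 | 10.6% | 6.4 | 16.2% |
| 90% | 11.3 | 19.2% | 12.7 | 27.8% |

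The assumed sensitivity drives the result. Across the table most arm 2 recipients of the message are truly negative.

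**Step 3: the primary endpoint.** It counts people tested by RDT and RNA and aware of their status. At the result visit, "The nurse will be in charge to confirm the awareness of testing status and to fill the CRF". A person with a false-negative DBS is still tested and informed, so the count does not change.

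**The case against.** The strongest reply is that this is a preference about phrasing. Section 3 reports WHO advice to perform RNA testing directly after positive serology, and the protocol does so. Section 3 calls DBS performance good and confines the sensitivity concern to low-level viraemia, whose frequency is not given. Refrigeration at the health centre and desiccant reduce the separate degradation risk. Treated patients are also told of their cure after one RNA test at week 24. The operation manual or the screening information sheet, neither of which is shown, may say more. And on the tentative agenda (first inclusion May 2022, six months of inclusion) many results would have been given before the July 2023 version.

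Much of this stands. It keeps the point small and rules out any criticism of the testing. It does not remove the point. The week 24 test is on plasma, to which the DBS caveat does not apply, and unseen documents do not undo wording that the protocol fixes. The re-infection warning may lead some people to seek a new test, so it would be too strong to say they have no prompt at all; but it does not mention a missed infection.

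A reader might infer more than the text supports:
- *That the algorithm needs a confirmatory test.* The reported WHO advice does not require one, and section 3 limits virological testing to some laboratories in Phnom Penh.
- *That the comparison is biased.* The primary endpoint is unaffected (step 3). Any loss of detected cases in arm 2 belongs to the RDT/DBS strategy under test (section 3, Study main hypothesis).
- *That the phrase about no consequences is wrong.* It describes the lifelong antibody, and nothing in the protocol contradicts it.
- *That the protocol contradicts itself at Visit W28*, where "Recommendations to continue liver ultrasound follow-up every 6 months will be given for cirrhotic patients". That advice addresses residual liver disease in cirrhotic patients after treatment, not a missed infection.
- *That arm 1 needs the same missed-virus caveat.* No text in the protocol supports this for plasma.

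**Conclusion.** The point holds as a minor patient-safety matter, worth considering. The prescribed message is more categorical than a single unconfirmed DBS result allows on the protocol's own account of that test, and following it as written would wrongly reassure any arm 2 participant with a false negative.

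The number of such participants cannot be derived. It is probably a handful: about 2 to 6 if overall sensitivity is 95% to 98%, and about 1 to 13 over the wider range of 90% to 99%. These figures rest on the assumed sensitivity, on viraemic shares from people with HIV, on 80% uptake, and on every antibody-positive person in arm 2 being tested and given a result. The testing algorithm, the sample size and the primary endpoint are not called into question.

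**What to change.** In section 9 (For negative HCV RNA patients), replace the statement of cure and of no need for follow-up or exams as follows.

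- Both arms: *No virus was detected in this sample, so no treatment or scheduled follow-up is needed now.*
- Arm 2 only, added: *A low level of virus can occasionally be missed, so ask for a new HCV RNA test if signs of liver disease or abnormal liver tests appear.*

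Keep the lifelong-antibody statement in full, and keep the re-infection warning. Schedule no repeat test.

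The cost is one or two sentences of text and a short briefing of the health-centre nurses, with no added test, sample, visit or analysis. The downside is a slightly less simple message for people who are mostly truly negative, and a person who later asks for an RNA test will have few places to get one. The change helps only those whose results are still to be given, unless the same counselling text is carried into a later roll-out.

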#### For positive HCV RNA patients

The nurse gives and explains the result to the participant and plan a visit in the Provincial Hospital in a short delay for liver disease assessment and treatment.

### **Liver disease assessment and treatment phase**

#### First visit in the Provincial Hospital (W0)

- Collect clinical data including:

- Socio-demographic: Gender, birth date, Ethnic origin, Profession, family situation, Level of income of the household, Contamination way, Liver diseases in the family
  - Drug abuse: Binge drinking, Alcohol dependence estimated by FACE questionnaire, Drug consumption and dependence
  - Anamnesis: Familial history of liver cancer, Personal history of liver disease, Vaccination HBV, Received Hepatitis C treatment in the past, was diagnosed as diabetics, Cardiovascular events, Current traditional medicine treatment
  - Co-morbidity: Metabolic syndrome, HIV infection, HBV infection,
  - Clinical examination: Weight, Height, BMI, Blood pressure, Proteinuria, Hepatic enlargement, Splenic enlargement, Ascites, Collateral circulation of the abdominal wall around the umbilicus, Encephalopathy, Ankle's edema, Extra hepatic signs
- Perform HIV and HBsAg RDTs
  - Collect biological samples and ask creatinine in emergency to get the result in one hour
  - Collect urine pregnancy test for women of childbearing age
  - Assess fibrosis level: APRI Score, Fibrosis-4 score (FIB-4). CHILD score for cirrhotic patients
  - Perform liver ultrasound: echostructure, Liver size, capsular contours, Liver nodules, Spleen size, Flow in the portal vein, Portosystemic shunt, Ascites
  - Explain and propose DAA treatment for non-symptomatic cirrhotic patients: dose, possible side effects, adherence
  - Give the prescription to the patient(monthly) and plan the next visit
  - Refer symptomatic cirrhotic patients to national hospital

### **Follow-up visit (from W0 to W12)**

From W0, the follow-up visit will take place at W4, W8 and W12.

During these visits, all patients will receive a clinical exam, an adherence counseling and an evaluation of adverse events (graded according to ANRS scale)

A blood sample will be done at W4 including complete blood count, AST/ALT and creatininemia.

A blood sample will be done at W8 and W12 including AST/ALT and creatininemia.

Urine pregnancy test for women of childbearing age will be done at W4 and W8.

### **Visit W24**

HCV RNA will be performed to evaluate the SVR12. In case of cirrhosis, CBC, PT, bilirubin, albumin will be done to evaluate the Child score and liver ultrasound will be performed to screen HCC.

### **Visit W28**

This visit will be the last visit of the study. In case of SVR12, patients will be informed of the cure. Recommendations to continue liver ultrasound follow-up every 6 months will be given for cirrhotic patients.

### **Procedure for non-responder's patients**

In case of treatment failure, patients will be referred to the National Hospital in Phnom Penh. HCV genotype and genome sequencing will be done in IPC and a Transient Elastography will be performed. A dedicated committee will evaluate the results and give a decision for therapeutic options.

